### Intervention

As described above and elsewhere, PPA is a password-protected, multifunction mobile app for supporting retention in HIV care and viral suppression [17]. Before clinical trial use, the color scheme and fonts were refreshed, the digital architecture of the app was evaluated and debugged to ensure reliability, and accessibility was upgraded to comply with Web Content Accessibility Guidelines (WCAG) 2.1 Level AA and Section 508 standards. All original app functions—that is, the article feed, first-person narratives, customizable reminders, local resources, community forum, and private chat function—remain organized as they were in the pilot study. A Positive Peers brand guide was created in the initial design phase by a professional marketing team to preserve PPA’s visual and content design. Informative articles are written by agency copywriters and study staff and are then vetted by clinicians. Participants are not directed or required to use the app in any specific way.

PPA is continuously monitored by a dedicated digital design team and PoPIT study staff. Conferences are held regularly to address issues identified by app administrators, reported by users, or noted by other study staff. The study coordinator relies on an electronic reporting system to alert the technical team, who respond promptly and effectively to app issues or bugs. PPA provides instructions for use, community standards, a privacy policy, and accessibility standards in an “About” tab within the app. All participants are made aware of data collection practices during informed consent. PPA does not sell or display advertising or rely on commercial sponsorships at this stage of development.

### Data Security and Accessibility

Existing infrastructure and security features of the PPA technology allow comprehensive and increasingly secure storage of PPA activity data. A centralized REDCap data management system is used to manage all study records and data. Unique modules are designed to securely store and track site recruitment, enrollment, informed consent and randomization, study questionnaires, qualitative interview participation, medical record review, EMAs, and study event reminders. All PPA usage data are stored on a secure, cloud-based, Health Insurance Portability and Accountability Act (HIPAA)– and System and Organization Controls 2 (SOC 2)–compliant server without any intrinsic ties to users’ demographic identities. Each study participant is assigned an ID upon enrollment, which is connected to their app and project activity. Questionnaire data are entered directly into and maintained in a secure REDCap database. PPA is compliant with WCAG for people with disabilities [73].

### Study Staff Training

The PoPIT study team delivers study training to staff at each collaborating site. Study staff at the trial sites reflect a range of expertise, with some highly trained in research support and others new to research work. The PoPIT training curriculum is organized into 3 parts: (1) orientation to the study, with emphasis on study staff roles and study flow (ie, prospective data collection); (2) specific instruction in the enrollment protocol, including review of study documents, consent, and randomization procedures; and (3) steps for downloading the PPA app and engaging with app functions. Staff new to research complete online basic research training through the host institution. PoPIT study instruction includes the formulation of a site-specific recruitment and promotion plan, as well as mock enrollment with PoPIT staff. The PoPIT study team conducts these trainings both in person and virtually, with an in-person session conducted at the site initiation visit. New site staff receive standardized onboarding in line with the training curriculum before actively enrolling participants in the study. Initial study training is supported by monthly site-specific videoconferencing meetings to reinforce the protocol and troubleshoot technical or other study-relevant problems. Tip sheets and notes supporting study procedures are maintained in a secure shared cloud storage system available to all study staff.

Site principal investigators and study staff meet monthly to discuss recruitment, best practices for patient enrollment, share successes and challenges, and troubleshoot issues. Concurrent with staff onboarding and site initiation, sites provide information to the PoPIT study team for integration into the PPA’s app infrastructure, including local contacts, logos, general information about the organization, and community resources that clinic staff wish to make readily available to their patient population. These resources include relevant medical clinics and contact information for local social service organizations. Many sites choose to include contacts for housing assistance, substance use and addiction support, mental health providers, food pantries, and support groups. These resources are transcribed into the app’s geographically organized resource database. All resources added to the database are independently verified by the PoPIT study team before being manually added to the app’s infrastructure.

### PPA Administrators

Each study site has a clinical study leader and a dedicated PPA administrator to carry out study activities. Some sites engage additional staff to support study-related activities such as recruitment, enrollment reporting, and medical record review. Study site PPA administrators receive separate training to maintain an online presence in the app that is welcoming but secondary to study participant interaction. For example, new participants are sent a welcome message by their site PPA administrator after entering the app. PPA administrators are asked to refrain from creating new posts in the community forum to avoid an administrator-dominated conversation, while commenting on posts when applicable. To date, as study enrollment has increased, PPA study app administrators have not initiated forum posts or discussions. Local PPA administrators are asked to maintain an unobtrusive presence in the app by introducing new users, providing occasional local or regional announcements, or engaging in private chats with participants to offer troubleshooting or technical support.

Generally, the PPA intervention is entirely user-directed and does not require additional human involvement. However, if the app is adopted as a clinical tool, a staff member at the clinic should be assigned to manage recruitment, registration, in-app support, and navigation services.

### Reminders and Notifications

The PoPIT study uses an automated alert and reminder system for follow-up questionnaire invitations. Reminders are keyed to each participant’s study enrollment date and study arm through the REDCap database system. Based on participant preferences, questionnaire invitations and reminders are sent via SMS text message or email. If contact information changes during the study, this is either reported directly by a participant to site staff or becomes apparent when a routine questionnaire invitation or reminder message is returned as undeliverable. Regular verification of contact information is emphasized to site staff as a critical component of project implementation and is continuously monitored. First, this routine outreach is an integral component of the PPA, functioning as an extension tool for clinical staff to promote engagement in care and support strategies outside the clinical encounter. Outside the trial environment, users receive notifications about updates and new features. Second, PPA includes a customizable notification system for the medication tracker, community forum, chat function, and event scheduling. Users can enable or disable these reminders and schedule the dates and times at which they are sent. Users may also opt in or out of notifications related to forum and chat activity. A third type of notification used in PPA is EMAs.

### Ecological Momentary Assessments

EMA is a method widely used to study behavior and mood in the settings in which they naturally occur [74,75]. Because of this immediacy, EMAs can support ecological validity by mitigating the memory limitations inherent in retrospective self-reports. Four general characteristics define EMAs: (1) data collection in real-world environments, (2) a focus on the individual’s current state of mind, (3) strategic selection of assessment moments, and (4) repeated assessments over time. Although the PPA records and maintains a log of each user action within the app, it remains unclear how users perceive the app while actively using it.

The PPA is premised on a user-centered model of digital media effects [59,61,63]. This approach suggests that users’ needs and the characteristics of the technology (ie, its affordances) interact to shape user engagement. Greater engagement with the mobile app is expected to influence self-efficacy in HIV management and increase the likelihood of favorable HIV clinical outcomes. As EMAs occur repeatedly in real time, they provide an opportunity to assess user engagement with the PPA more immediately than retrospective self-report. The goal of the EMA methodology is to link tracked physical interactions with the app (ie, natively recorded usage data) to users’ immediate perceptions of engagement in real time.

User engagement with interactive media comprises 4 validated attributes: (1) physical interaction, (2) interface assessment, (3) absorption, and (4) digital outreach [76]. Analyses indicate that greater physical interaction with the app and more positive assessments of the interface predict cognitive absorption with the content, which in turn is associated with stronger behavioral intentions to manage and socially share the content [76]. Our conceptual model has focused primarily on frequencies of physical interaction. EMAs can provide insight into user perceptions of the app interface and the extent to which users feel absorbed or attentive during use. We may also include a single-item measure of digital outreach in the form of the likelihood of recommending the app to others. Ultimately, we anticipate that increased user engagement will be associated with higher medication adherence, lower viral load, greater engagement in care, and reduced stigma. In this study, EMAs are delivered as SMS text messages sent to participants. The first EMA is deployed to all users 1 month after they begin using the app and focuses on physical interaction with the PPA (see Table 2). The second EMA is sent 2 months after app initiation and includes brief questions assessing current participant engagement with the PPA interface, as well as 4 items adapted from the System Usability Scale [77]. These micro-questionnaires serve as evaluative tools for assessing intervention implementation and effectiveness.

**Table 2 table2:** EMA^a^ items at time 1 and time 2.

EMA items			Response option
**Time 1 EMA items: interaction with the PPA^b^**			
	Is the Positive Peers mobile app downloaded to your smartphone right now?	Yes/no	
	Did you use the Positive Peers mobile app today?	Yes/no	
	How many days in the last week did you use the Positive Peers mobile app?	Daily 4-6 days 2 or 3 days Once None	
	Did you take your medication yesterday?	Yes/no	
**Time 2 EMA items: interface assessment, absorption, and digital outreach**			
	When was the last time you used the Positive Peers app?	I haven’t used the Positive Peers app. Yesterday or today Within the last week Within the last month	
	In general, the app is interesting to me.	Strongly agree to strongly disagree	
	This app holds my interest.	Strongly agree to strongly disagree	
	While I was using the app, I was able to focus on the task at hand.	Strongly agree to strongly disagree	
	I would recommend this app to other people like me.	Yes/no	

^a^EMA: ecological momentary assessment.

^b^PPA: Positive Peers mobile app.

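### The 2-month EMA's last-use item has no answer for a participant who used the app in month 1 and then stopped

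*Protocol article*

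**What the plan says.** The Ecological Momentary Assessments section sets the timing of both waves from each participant's start on the app. For the first: "The first EMA is deployed to all users 1 month after they begin using the app". For the second: "The second EMA is sent 2 months after app initiation". On the channel: "In this study, EMAs are delivered as SMS text messages sent to participants".

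Table 2 gives the Time 2 items. The first asks "When was the last time you used the Positive Peers app" and offers four answers: "I haven’t used the Positive Peers app", followed by "Yesterday or today Within the last week Within the last month". Three agreement items on interest and focus and a yes/no item on recommending the app come after it.

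The same section explains why EMAs are used: "As EMAs occur repeatedly in real time, they provide an opportunity to assess user engagement with the PPA more immediately than retrospective self-report". It gives their goal as linking natively logged use to "users’ immediate perceptions of engagement in real time", and it treats the two micro-questionnaires as tools for evaluating implementation and effectiveness.

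App use is also measured independently. Table 3 and the PPA Engagement section say that logins, minutes, sessions and function counts are recorded natively in real time and tied to the study ID.

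**The concern.** A question about last use needs answers that cover every possible date back to the start of use. This one is asked at 2 months and looks back 1 month. Participants who tried the app early and then stopped fall outside every dated option, and they are the people a study of engagement most needs to identify.

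Their answers go wrong in opposite directions. Choosing the never-used option makes a lapsed user look like someone who never started; choosing the last-month option makes the same person look current. The never-used category also becomes hard to read. The survey clock starts at app initiation, so some who tick it may mean no use at all and others may mean no recent use.

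The interest, focus and recommendation ratings are collected at this wave only. If they are tabulated by the self-reported recency answer, both the never-used and the last-month groups will contain lapsed users.

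**Working it through.** The article states no figure for this point, so there is nothing to reproduce. The check is whether the printed answers cover all possible last-use dates.

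**Inputs**
- Time from app initiation to the second EMA: 2 months, taken as T = 60, 61 or 62 days (Ecological Momentary Assessments).
- Longest dated option: within the last month, taken as m = 28, 30 or 31 days (Table 2, Time 2 items).
- The only other option: never used (same item).

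**Method**
- For someone who has used the app at least once, days since last use can be any whole number d from 0 (survey day) to T (initiation day), which is T + 1 values.
- The dated options cover d = 0 to m. The never-used option is untrue for all of these people.
- Uncovered values: T − m. Uncovered share: (T − m)/(T + 1).

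**Results**

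| T (days) | m (days) | Uncovered values, T − m | Possible values, T + 1 | Share |
|---|---|---|---|---|
| 60 | 31 | 29 | 61 | 47.5% |
| 61 | 30 | 31 | 62 | 50.0% |
| 62 | 28 | 34 | 63 | 54.0% |

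The first and last rows are the extremes over all combinations of T and m. About half of the possible last-use dates, 48% to 54%, therefore have no truthful answer. To turn this into a share of respondents, one would need the distribution of last-use dates and the response rate among lapsed users. The article gives neither.

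**Timing against purpose**
- Purpose: immediate perceptions, linked to logged use in real time.
- Design: one SMS at 1 month and one at 2 months, sent at a fixed interval from app start whether or not the participant is using the app.
- The Time 2 focus item is in the past tense and names no session. A rating coincides with use only if the participant happened to be using the app at about the time the message arrived.

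**Where true use can still be found**
- The EMA section says the app keeps a log of each user action, and the PPA Engagement section ties tracked use to the study ID. A last-use date should therefore be recoverable for each respondent.

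**The case against.** The strongest reply is that the study does not rely on this item to measure use. Engagement is defined from the native log, and someone who stopped after month 1 is visible there whatever they tick. The EMA is meant to be read alongside that log. No EMA item is named as an outcome or in the planned analysis. This stands, and it confines the harm to the item itself and to perception scores grouped by it. A reader might infer that early lapse is lost to the study; the documents do not support that.

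A second reply is that fixed-time prompting is a legitimate EMA design and that Time 1 has near-momentary content: whether the app is on the phone now, whether it was used that day, and a weekly frequency item with a none option. This also stands. A reader might infer that no real-time link is obtained at all. That goes too far, because a response given on a day of use can be matched to the log. What remains is that the wording promises perceptions during active use and the schedule does not aim at such moments.

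A third reply is that the article condenses the instrument. The System Usability Scale items mentioned in the text are not identified in Table 2, and skip logic or a not-applicable option may exist in the full instrument. That is fair, so the absence of routing is not held against the plan. The reply does not rescue the last-use item, whose answer list is printed.

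**Conclusion.** The point holds as a small, definite defect in one self-report item. As printed, the Time 2 last-use question cannot be answered truthfully by a participant whose last use was more than a month before the survey. That gap spans about half (48% to 54%) of the possible last-use dates, assuming 60 to 62 days to the survey and a month of 28 to 31 days.

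A reader might take that figure as the share of participants misclassified. It is not: the article gives no lapse rate, so the number affected cannot be estimated from it.

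The randomized comparison of viral suppression and retention is untouched, and log-based engagement measures remain correct. What is affected is the self-reported recency variable and any reading of the interest, focus and recommendation scores by it. The description of the two waves as real-time capture is generous for SMS surveys sent at fixed times. This is an inexpensive improvement to a secondary implementation measure.

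**What to change.** 1. Add 'More than a month ago' to the Time 2 last-use item.
2. For responses already collected, classify last use at the survey date from the native log. Use action-level records, because the monthly aggregated reports described under PPA Engagement may be too coarse to date last use.
3. When interpreting the interest, focus and recommendation items, group respondents by log-based last use. Keep lapsed users' ratings and report them separately from current users'. Hiding these items from lapsed users, or sending them only after a logged session, would remove the views of the people who disengaged, so neither is proposed.
4. Describe the two SMS waves as brief fixed-time surveys linked to the usage log, rather than as perceptions captured during active use.

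The cost is one response option, a sentence or two of text, and a log extraction. The downside is a response set that changes partway through the study, with earlier answers recoded from the log.

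The change can still reach later participants. Accrual runs to November 27, 2026. Someone enrolled that day would reach the Time 2 EMA about 2 months later in the immediate arm (late January 2027), or about 6 + 2 = 8 months later in the delayed arm (late July 2027).

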### Quantitative Data Collection and Measures

Data collection is planned for a total of 18 months for each participant. Three modes of data collection are used in the study. First, site staff collect medical record data, including date of diagnosis, HIV viral load, T-cell counts, and office visit dates, for the 12 months before enrollment and for 18 months after enrollment.

Second, participants receive an email or SMS text message notification to complete follow-up electronic questionnaires at 3, 6, 9, and 12 months after enrollment. Automated reminders are sent on the scheduled completion date; if the questionnaire is not completed, additional reminders are sent 1 week and 2 weeks later. If the questionnaire coincides with an office visit or cannot be completed remotely for any other reason, study staff can administer the pending questionnaire on site using a laptop or iPad (Apple Inc). Delayed-start participants are onboarded to the app, either in person or remotely by site staff, 6 months after enrollment. This group completes baseline, 3-month, and 6-month questionnaires before downloading and initiating app use.

Third, during the intervention period, EMAs are used to collect in-the-moment information about app use (eg, “Is the Positive Peers mobile app currently downloaded to your phone?”) and related perceptions. PPA provides a natural technological interface through which such perceptions or behaviors, and their correlates within the app or the broader social environment, can be assessed in a nuanced, dynamic, and longitudinal framework.

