Allocation (1:1) to study conditions is determined by the REDCap system’s randomization module following signed consent and completion of the baseline questionnaire, and before PPA download. Participants are informed of their randomization assignment after completing the baseline questionnaire. If randomized to the immediate intervention condition, site staff assist the participant in downloading the PPA to their personal smartphone and orient them to the app’s functions and study guidelines. Participants randomized to the delayed-start arm receive usual clinic care before returning to the clinic 6 months later to download and begin using the app. This delayed-start cohort serves as a control group, allowing comparison of the effects of intervention exposure with usual care.

The Practical Robust Implementation and Sustainability Model (PRISM) was used to inform intervention implementation throughout the study [70,71] (Table 1). The PRISM model was selected because it accommodates multilevel and dynamic interactions among the intervention, stakeholders’ perspectives, and recipient characteristics. The PRISM model is an expansion of the well-used RE-AIM (ie, Reach, Effectiveness, Adoption, Implementation, and Maintenance) approach, with additional emphasis on sustainability factors both within and external to the study setting [70].

**Table 1 table1:** PRISM^a^-informed implementation plan for the PoPIT^b^ study.

RE-AIM^c^ domain	Before implementation	During implementation	After implementation
Intervention delivery	Estimate population parameters with site staff and set accrual benchmarks. Develop recruitment strategies with site staff.	Log and monitor recruitment and enrollment. Deploy boosting efforts if needed.	Calculate reach and enrollment trajectories.
Effectiveness	Preintervention site visits to determine setting and population characteristics, and resources.	Collect prospective questionnaire data. Medical record review. Conduct user qualitative interviews.	Primary and secondary outcome analysis and qualitative analysis of user interview data.

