### Enrollment, Randomization, and Data Collection Procedures

All participants are consented, enrolled, and randomized at the partner institution where they receive care, in partnership with the PoPIT staff, who are needed to set up the user’s PPA account. Specifically, following in-person consent at the partner site, all participants complete a preloaded baseline questionnaire on a study-dedicated tablet in the presence of study staff. While they are completing the questionnaire, the trial participant is randomly assigned in REDCap to either the intervention (immediate PPA start) or control (6-month delayed PPA start) arm at a 1:1 ratio. Participants randomized to the delayed-start arm receive usual clinic care before beginning the clinical intervention. Given our pilot findings indicating a stronger PPA effect on HIV viral suppression among participants in the youngest age group (ie, <24 years), we employ a block randomization strategy in which study arm assignment occurs separately for participants within the age groups 13-24 and 25-34 years.

Following randomization, site study staff assist participants randomized to the immediate-start arm in downloading the PPA from the public app store using the participant’s personal phone. Site study staff guide participants through in-app tutorials demonstrating how to use app features. Participants randomized to the delayed-start arm are provided with a folder containing general HIV self-management information and contact numbers for the clinic and the site coordinator. Data are collected via online forms (enrollment and medical record review), questionnaires, and SMS text messaging. Participants are consented and enrolled by study staff in person, and the baseline questionnaire is completed independently at the same visit. Remaining follow-up questionnaires at 3, 6, 9, and 12 months are prompted by an SMS text message or email and completed online. Participants and study staff are aware of study arm assignment. Delayed-start participants are given app access after completing the 6-month questionnaire. Site study staff follow the same procedure to assist with downloading the app and reviewing tutorials for participants in both the immediate- and delayed-start arms.

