### Planned Statistical Analysis

Aims 1 and 2 entail data collection and analysis to provide evidence of PPA effectiveness. Outcomes include retention in HIV care (proportion of enrolled patients with laboratory results in each 6-month period of the study), HIV load suppression (proportion of enrolled patients whose viral load measurement at 6 months in the study is <200 copies/mL), as well as self-reported psychosocial variables, specifically perceived technology affordances, attitudes toward technology, and self-efficacy for managing chronic conditions. We expect that key demographics, technology covariates, and PPA use will predict self-efficacy, which will be directly associated with (1) retention in care, (2) viral suppression, and (3) HIV-related perceived stigma. Additionally, we plan to test potential covariate mediation and examine theoretical linkages in our model of PPA effects.

Analyses of repeated measures will be performed using generalized linear mixed-effects models with a logit link function for binary outcomes (ie, viral suppression and engagement in care) and linear mixed-effects models for continuous outcomes (eg, perceived stigma, resilience). Time will be treated as a fixed, repeated factor within patients, and patient-specific random effects will be included to account for within-patient correlation. To appropriately model the hierarchical structure of observations nested within patients and patients nested within sites, the site will be included as a random effect, providing an estimate of between-site variability. Multilevel mediation models will be used to evaluate potential mediating effects of covariates. *P* values will be adjusted using Bonferroni or Benjamini-Hochberg correction procedures to control the family-wise type I error rate due to multiple comparisons across distinct psychological outcomes.

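### On-site completion of the month-6 self-report scales may differ by arm, because only the delayed arm has a planned staff contact then, although the plan promises identical assessments

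*Protocol article*

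**What the plan says.** All references are to the Protocol article.

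- **Promise of equal treatment.** Study Design states that procedures and assessments are the same in both arms for the first 6 months and that only the timing of app access differs. It names month 6 as the primary randomized comparison.
- **Baseline.** Under Enrollment, Randomization, and Data Collection Procedures, "all participants complete a preloaded baseline questionnaire on a study-dedicated tablet in the presence of study staff". The same section adds that "the baseline questionnaire is completed independently at the same visit".
- **Follow-up.** The default in both arms is remote: "Remaining follow-up questionnaires at 3, 6, 9, and 12 months are prompted by an SMS text message or email and completed online".
- **On-site fallback.** Quantitative Data Collection and Measures says: "If the questionnaire coincides with an office visit or cannot be completed remotely for any other reason, study staff can administer the pending questionnaire". This takes place at the clinic, with a laptop or iPad. The sentence names no arm and no time point.
- **Month 6 in the delayed arm.** Study Design says these participants "receive usual clinic care before returning to the clinic 6 months later to download and begin using the app". Quantitative Data Collection and Measures says: "Delayed-start participants are onboarded to the app, either in person or remotely by site staff, 6 months after enrollment". The enrollment section gives app access only once the 6-month questionnaire is done.
- **Blinding.** Participants and staff know the assignment.
- **Within-arm change.** Study Design attributes improvement in the delayed arm before month 6 primarily to nonspecific effects of being in the trial.

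**The concern.** Perceived stigma is a named outcome, and the analysis section makes self-efficacy the expected route to retention, suppression and stigma. These are sensitive self-reports in an open-label trial. Answers given in clinic, with staff who know the arm nearby or administering the form, may differ from answers given privately online.

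If the share completed on site at month 6 differs between arms, the arm contrast on these scales includes a difference in mode as well as any effect of the app. The schedule gives a reason to expect such a difference. A delayed-arm participant who comes in for app start with the questionnaire still pending has an obvious on-site route and an incentive to use it, because access depends on completion. No corresponding month-6 study contact is described for the immediate arm.

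On-site completion in either arm also depends on attending clinic, and office visits define engagement in care. Mode can therefore depend on something the app is meant to change.

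**Working it through.** **1. The plan's own figure.** The only sample-size figure is 106 per arm for viral suppression, 0.60 versus 0.80, two-sided 0.05, 90% power. With unpooled variance, n = (1.960 + 1.282)² × (0.60×0.40 + 0.80×0.20) / 0.20² = 105.07, so 106. With pooled variance n is 109, and power at 106 is 0.894. The figure is reproduced closely enough and is not at issue. It is used here only to set a standard error. The article gives no figure for the self-report scales or for mode.

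**2. Inputs for the illustration.** All are assumptions except n.
- m: mean shift between on-site and remote completion, 0.1 to 0.3 SD.
- d: on-site share at month 6 in the delayed arm minus that in the immediate arm, 0 to 1.
- n = 106 per arm.

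**3. Formulas.** Bias in the month-6 arm contrast = m × d. Standard error of a standardized difference = √(2/106) = 0.137. Type I error = P(|Z + bias/0.137| > 1.96).

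| m (SD) | d = 0 | d = 0.25 | d = 0.50 | d = 1.00 |
|---|---|---|---|---|
| 0.1 | 0; 0.050 | 0.025; 0.054 | 0.05; 0.065 | 0.10; 0.113 |
| 0.2 | 0; 0.050 | 0.05; 0.065 | 0.10; 0.113 | 0.20; 0.307 |
| 0.3 | 0; 0.050 | 0.075; 0.085 | 0.15; 0.194 | 0.30; 0.589 |

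Each cell gives bias in SD, then type I error. For the bias to reach one standard error, d must be 0.137/0.2 = 0.69 at m = 0.2, or 0.137/0.3 = 0.46 at m = 0.3. At m = 0.1 it cannot. With 125 per arm (half of the 250 to be randomized), the type I error at m = 0.2 is 0.068 for d = 0.25 and 0.124 for d = 0.50.

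**4. Baseline to follow-up.** The move from clinic tablet to remote completion applies to both arms. If the on-site shares are equal, d = 0, the bias is 0 and the type I error stays at 0.050 for any m. Within an arm, the change from baseline contains a shift of m × (1 − on-site share at follow-up), if on-site follow-up resembles the baseline setting. With an assumed delayed-arm share of 30% to 80%, this is 20% to 70% of m: 0.02 SD (0.1 × 0.2) to 0.21 SD (0.3 × 0.7).

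**The case against.** The strongest reply is that nothing in the plan sends the delayed arm to on-site completion. The fallback is permissive, covers either arm and any follow-up, and leaves online as the default. Onboarding may be remote. The questionnaire precedes app access, with reminders on the due date and 1 and 2 weeks later, so it can be finished online before any visit. Immediate-arm patients may also be in clinic near month 6, since viral load is typically required at least every 6 months. Baseline is self-completed electronically, so what changes is mainly setting and staff presence. All of this stands, and it limits the point to a possible imbalance.

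A reader might infer four stronger things that the article does not support:
- That mode is confounded with arm by design. It is not: on-site completion is optional and names no arm.
- That the switch from clinic tablet to remote completion biases the randomized comparison. It is common to both arms and cancels.
- That within-arm change carries nearly the whole mode effect. That cannot be combined with substantial on-site completion at month 6, as step 4 shows.
- That the absence of a mode term from Planned Statistical Analysis is a defect. The full analysis plan is not shown, so it is no finding.

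The objection does not remove the conflict between a stated return to clinic, onboarding that may be remote, and a promise of identical assessments. Nor does it remove the only planned month-6 staff contact, which falls in one arm.

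**Conclusion.** The concern holds in a limited form. The month-6 assessment is not guaranteed identical across arms, because one arm has a staff contact tied to completing the questionnaire and unblinded staff may administer it on site. The risk is confined to stigma, support, self-efficacy and any other self-report taken then. Retention and viral suppression come from medical records and are unaffected.

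On an assumed 0.2 SD mode effect and a 25- to 50-point imbalance, the bias is 0.05 to 0.10 SD, less than one standard error. Both inputs are assumptions. The direction is unknown: if staff presence draws more favourable answers, the delayed arm looks better and the bias runs against the app; if it draws less favourable ones, the bias favours the app.

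Separately, the change of setting after baseline is a further explanation for within-arm change in self-reports, beside the nonspecific trial effects to which Study Design primarily attributes it. This is a cheap improvement to a stated procedure, not a threat to the clinical outcomes.

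**What to change.** 1. Reconcile the two descriptions of delayed-arm app start (Study Design; Quantitative Data Collection and Measures) with the statement that assessments are identical to month 6.
2. Have both arms self-complete the month-6 questionnaire through the personal link, the delayed arm before its onboarding contact. This keeps the existing order of questionnaire first, then access.
3. Where on-site completion is unavoidable, the participant self-completes privately on the device.
4. Record mode in REDCap at every questionnaire (remote, on-site self-completed, staff-administered) and report it by arm.
5. Treat any remote-only analysis as supportive, because it selects on a post-randomization variable.
6. When within-arm change in self-reports is interpreted, name the change of setting as one explanation.

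The cost is one extra field, changed site instructions, and slightly earlier or later completion of some month-6 questionnaires. Accrual runs to November 2026, so the change can still cover later participants. Mode that is not logged at the time may be impossible to recover.
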